### Primary and secondary outcome measures

The main outcome measure, the change in number of drinks consumed in the past 14 days three months after the intervention compared to baseline, will be assessed using the TLFB method [35]. Secondary outcome measures are: changes in automatic cognitive biases as assessed with the attentional bias, alcohol/no-go and approach bias tasks described above. Generalisation effects of attentional bias and approach bias training to other measures will be assessed with the alcohol Stroop task (described above) and the brief Implicit Association Task (bIAT, [47,48]), which is used to measure the strength of both approach associations and positive (valence) associations with alcohol. In the bIAT, participants are required to decide whether or not the exemplar word in the middle of the screen belongs to one or two focal categories at the top of the screen, by pushing the designated ‘yes’ or ‘no’ buttons (‘e’or ‘i’) on the keyboard. As in the study of Menatti et al. [47], the typical 7 block structure of the IAT was maintained, but with fewer trials per block. In the first block (12 trials) names of alcoholic (wine, beer, vodka) or non-alcoholic drinks (coke, water, juice) have to be classified as either belonging to the category ‘alcohol’ or not. In the second block (12 trials) exemplars have to be classified as either pleasant (funny, cheerful, sociable) or not (nauseous, sad, tired). In the third block (12 trials) and fourth (24 trials), the target (alcohol) and attribute (pleasant) categories are combined. In the fifth block (12 trials), the reversed attribute category, unpleasant, is practiced and then combined with the target category (alcohol) in the sixth (12 trials) and seventh block (24 trials). The approach bIAT follows the same structure, with the attributes ‘approach’ (grab, touch, take) ‘avoid’ (let go, avert, ignore). The order of the two versions of the bIAT, as well as the order of the combined blocks within the bIAT, and the contingency between the response (yes/no) and the buttons (i/e) is counterbalanced across participants. The outcome measure is the standardised difference in latencies (*D* score*)* between the different combined blocks.

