### Sample size

G*Power 3.1.5 [54] was used to calculate the sample size for a power of 0.8 for each main effect or interaction (all Numerator *df* = 1), at an alpha of 0.05. Based on a meta-analysis of internet self-help interventions for problem drinkers a medium effect size (*f* = 0.25) would be expected [2], but the effect size may be reduced by the active control conditions and the two modules of the *DrinkingLess* intervention that all participants receive. A small-to-medium effect size of *f* = 0.15 was therefore specified, for which the required sample size is 351 (see Figure 7).

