### Randomisation

Participants meeting the inclusion criteria will be automatically assigned to one of the 8 intervention conditions with an equal likelihood, using the method of minimisation [55] in order to balance for gender and AUDIT risk level (scores 8–19 versus >19). Participants will be randomly allocated to one of the conditions to which the fewest participants of their gender and AUDIT level have so far been assigned. Intervention allocation will be corrected for excluded participants. Participants will be excluded if (a) they do not complete the baseline assessment including *DrinkingLess*, or (b) if they indicate that they want to discontinue the study.

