### Clinical evaluation

All analyses will be conducted in agreement with the intention to treat principle, as per the CONSORT statement [56]. To that end, missing endpoints will be imputed using the EM algorithm [57]. The main effects and interaction effects of the CBM interventions on the primary and the continuous secondary outcome measures will be analysed with a 2 (attentional bias retraining: active/placebo) × 2 (alcohol/no-go training: active/placebo) × 2 (approach bias retraining: active/placebo) × 2 (time: pre-intervention/3 month follow-up) repeated measures ANOVA.

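### Exclusion of assigned participants who announce withdrawal has no time limit; read plainly it conflicts with intention to treat, and it makes later allocation depend on withdrawal

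*Protocol article*

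**What the plan says.** Three statements in the protocol article bear on this point.

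- **Who is assigned (Randomisation).** "Participants meeting the inclusion criteria will be automatically assigned to one of the 8 intervention conditions with an equal likelihood", by minimisation on gender and AUDIT risk level. A new participant goes at random to one of the conditions with the fewest people so far in the same gender and AUDIT group.
- **Who is then excluded (Randomisation).** Rule (a) covers people who do not complete baseline including DrinkingLess. The second rule reads "b) if they indicate that they want to discontinue the study". The section also states: "Intervention allocation will be corrected for excluded participants".
- **How the data are analysed (Clinical evaluation).** "All analyses will be conducted in agreement with the intention to treat principle, as per the CONSORT statement", and to that end "missing endpoints will be imputed using the EM algorithm".

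The primary outcome is "the change in number of drinks consumed in the past 14 days three months after the intervention compared to baseline". The article does not say whether people excluded under rule (b) stay in the analysis set, nor up to what point rule (b) applies.

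**The concern.** Rule (a) ends before any CBM is given, so it should not depend on the assigned condition. Rule (b) is tied to no point in time. As worded it also covers the roughly five weeks of training and the follow-up, when a wish to stop can depend on the version of training received.

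Removing such people is not intention to treat, and imputation cannot reach someone who is no longer in the set. Two participants with the same course would be handled differently according to whether they sent a message.

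If announced withdrawal differs between the active and placebo versions of a task, and those who withdraw drink more or less than those who stay, the retained groups are no longer the randomised groups and the main effect of that task could be biased. Separately, lowering the minimisation counts after a withdrawal steers a later matching enrollee into the condition that lost someone.

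**Working it through.** **1. The passages side by side.**

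| Participant after CBM has started | Randomisation, plain reading | Clinical evaluation |
|---|---|---|
| Stops silently | Not covered by rule (b) | Kept, endpoint imputed |
| Says they want to stop | Excluded, count corrected | Kept, endpoint imputed |

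The second row cannot be carried out both ways unless *excluded* means something narrower than it says.

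**2. The plan's own figure.** Inputs from Sample size: f = 0.15, alpha 0.05, power 0.8, numerator df 1; eight groups. With the noncentral F distribution, df2 = N − 8 and λ = N·f². At N = 351, λ = 351 × 0.0225 = 7.90 and power is 0.8002, and this is the smallest N that reaches 0.80. The stated 351 is reproduced. For a two-level factor d = 2f = 0.30 SD, which is the yardstick below.

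**3. Possible bias from removing announced withdrawers.** The article gives no withdrawal rates, so every rate and gap here is an assumption. The true effect is set to zero. Let p be the announced-withdrawal rate at one level of a factor, and g the amount, in SD, by which withdrawers drink more than stayers. The whole-group mean is (1 − p)·stayers + p·(stayers + g), so the stayers' mean lies p·g below it. The spurious benefit is therefore (p_active − p_placebo)·g. With 351 retained, the shift in z is the spurious benefit × √351 / 2.

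- 20% v 10%, g = 0.5: 0.10 × 0.5 = 0.05 SD, or 17% of 0.30. The z shift is 0.05 × 18.73 / 2 = 0.47, and a nominal 5% test rejects about 7.5% of the time.
- 30% v 15%, g = 0.8: 0.15 × 0.8 = 0.12 SD, or 40% of 0.30. The z shift is 1.12, and the test rejects about 20% of the time.
- Equal rates and equal g: 0 SD, rejection 5%.

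**4. Cross-check with another selection model.** Let those with the poorest expected change leave, with correlation ρ between the tendency to withdraw and the outcome, and no replacement. The retained mean shifts by ρ·φ(Φ⁻¹(p))/(1 − p).

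- 20% v 10%, ρ = 0.3: bias 0.046 SD, type I error 0.069.
- 30% v 10%, ρ = 0.5: bias 0.151 SD, type I error 0.241.
- 20% v 20%: bias 0, type I error 0.05.

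**5. The allocation correction.** 351 / 8 is about 44 per cell. To hold 44 retained at 20% v 10% withdrawal, 44 / 0.8 = 55 and 44 / 0.9 = 49 would have to be assigned. This shows how far assignment would follow withdrawal; it does not measure bias. Refilling restores N but does not undo the selection.

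**The case against.** The strongest counter-argument is that nobody is said to be deleted from the analysis. The rule stands under Randomisation, directly after the sentence on correcting the allocation, so *excluded* may mean only taken out of the minimisation counts, with Clinical evaluation governing the analysis. Rule (b) is also paired with a rule that acts only before CBM, so a pre-training meaning is possible. Both readings are open, but neither is written down. The first would still leave the counts being corrected with no time limit.

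The objections to the size carry more weight:

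- Rule (b) reaches only people who announce that they want to stop. The Discussion expects high attrition in general and says nothing about announced withdrawal. Silent dropouts are kept on either reading.
- The two levels of a factor differ only in the contingency within one of three tasks. Session length is the same and participants are blinded by responding to an irrelevant feature. A twofold difference in announced withdrawal is therefore unlikely, though blinding does not exclude it.
- Keeping withdrawers in the set would not remove all of the computed bias. If they refuse the 3-month measure and differ from stayers with the same observed data, EM fills in the stayers' expected value and the difference remains. The rule's own contribution is the part that could be recovered from withdrawers who still give data, or explained by observed data.
- A new enrollee's assignment depends on earlier counts, not on that person's prognosis. The effect of the count correction has not been estimated.

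All four points stand.

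**Conclusion.** The point holds as a conflict of wording with a possible, unquantified bias. Read plainly, an exclusion after assignment without a time limit does not fit with "All analyses will be conducted in agreement with the intention to treat principle" and imputed endpoints. On the narrower reading, the count correction still makes later assignment depend on withdrawal after assignment.

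The size is unknown. The 0.05 and 0.12 SD are upper limits on what the rule could contribute at the assumed rates and gaps, and not forecasts. They require announced withdrawal to differ by condition, in rate or in kind, and to be related to drinking. Without such a difference there is no bias.

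A reader might infer that withdrawers will certainly be dropped from the primary analysis, or that the rule itself distorts the result by 17% to 40% of the planned effect. The article supports neither: it does not define the analysis set for these people, and it gives no withdrawal rates. The wording should be settled because the repair is cheap and outcome data not requested at the time may not be recoverable. It does not by itself invalidate the primary comparison.

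**What to change.** In Randomisation:

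1. Limit both the exclusion and the correction of the minimisation counts to the period before the first CBM session is released to the participant.
2. State that everyone released to CBM stays in the intention-to-treat set in the assigned condition, whatever they later say about stopping.

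In Clinical evaluation:

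3. State that the 3-month TLFB is still requested from those who stop training. If they refuse, the endpoint is missing and handled by the planned method.
4. Report announced withdrawals by condition.

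The cost is a few sentences and one change to the allocation script. The downside is a few more missing endpoints and slightly uneven cell sizes. The sample size of 351 does not change.

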### Blinding

Outcome assessments are inherently blinded, since they occur online, thus in the absence of assessors and researchers. In order to keep participants blind to their intervention condition, participants are required to respond to an irrelevant feature in all CBM interventions (e.g. the format of the picture) instead of the content of the picture (alcoholic or non-alcoholic beverage). Participants’ awareness of intervention condition is assessed at the post-intervention measurement.

### Clinical evaluation

All analyses will be conducted in agreement with the intention to treat principle, as per the CONSORT statement [56]. To that end, missing endpoints will be imputed using the EM algorithm [57]. The main effects and interaction effects of the CBM interventions on the primary and the continuous secondary outcome measures will be analysed with a 2 (attentional bias retraining: active/placebo) × 2 (alcohol/no-go training: active/placebo) × 2 (approach bias retraining: active/placebo) × 2 (time: pre-intervention/3 month follow-up) repeated measures ANOVA.

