## Methods/design

### Trial design

The (cost) effectiveness of attentional bias retraining, alcohol/no-go training, and approach bias retraining will be studied in a 2×2×2 factorial design. This will allow us to explore possible additive or multiplicative effects of different combinations of CBM, as well as the related question to what extent retraining one bias will produce changes in other automatic biases; issues which not only have clinical relevance, but also important theoretical implications (see for example [28,29]). Participants will receive either the active or the placebo version of all three CBM interventions, amounting to eight conditions (see Figure 1). Prior to the training, participants will complete the first two modules of the *DrinkingLess* program [25]*.* Intervention effects will be tested directly after the intervention and 3, 6 and 12 months later. The expected timeline for trial completion and reporting the results is presented in Figure 2.

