The main strength of this study is also its main limitation: the effectiveness of CBM might be threatened by its web-based delivery. First, the less controlled home environment might pose several distractions, both online (incoming e-mails, other browser windows), and ‘offline’ (television, phone calls), which could confound the RT-based CBM interventions. To this end, participants are reminded at the start of each CBM session of the importance of concentration for the effectiveness of the training. The feasibility of web-based CBM is supported by a recent study on attentional bias retraining in social anxiety, which found error rates and reactions times comparable to those in a lab-based setting, though no evidence was found of training effects [61]. Second, online interventions are commonly faced with high attrition rates [62]. Therefore, treatment adherence is encouraged in five ways: 1) by automatic e-mails that are sent to invite and remind participants of CBM sessions 2) the possibility of e-mail contact with the first author in case participants have questions or encounter technical difficulties 3) the attention that was paid to the intervention rationale 4) the inclusion of motivating features to the CBM interventions 5) a lottery system in which participants who complete the follow-up assessments can win gift vouchers. Taken together, the possible threats presented by the web based setting of this study are outweighed by the possibilities offered by internet-delivered CBM, which, if proven effective, could easily be implemented as a low threshold, early intervention for problem drinkers.

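### Filling missing endpoints by EM and then running an ordinary ANOVA either inflates type I error or dilutes the effect, depending on an imputation model the protocol does not state

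*Protocol article*

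**What the plan says.** The Clinical evaluation section sets the aim ("All analyses will be conducted in agreement with the intention to treat principle"), the means ("missing endpoints will be imputed using the EM algorithm [57"]) and the analysis of the primary and continuous secondary outcomes: a factorial model of the three trainings, each active or placebo, by time ("time: pre-intervention/3 month follow-up) repeated measures ANOVA"). It attaches no multiple imputation, pooling rule or other variance correction. The bootstrap and sensitivity analyses described under Economic evaluation concern the cost-effectiveness results only.

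The primary outcome is "the change in number of drinks consumed in the past 14 days three months after the intervention compared to baseline". The Sample size section plans "for a power of 0.8 for each main effect or interaction", "at an alpha of 0.05", with f = 0.15, giving 351 participants. It states no allowance for dropout. The Discussion warns that "online interventions are commonly faced with high attrition rates [62"] but gives no expected rate.

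**The concern.** EM gives sound maximum-likelihood estimates of means and covariances. Using it to fill in individual endpoints and passing the result to an ordinary ANOVA is a different procedure. The filled values are conditional means: they carry no residual scatter and no uncertainty about the fitted model. The ANOVA nevertheless counts each one as a measured endpoint, both in the error variance and in the error degrees of freedom.

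What follows depends on whether the imputation model contains the training factors. With them, the effect estimate is sound but its standard error is too small, so a training could be declared effective too often. Without them, participants with missing endpoints get values that do not differ by training, and the effect is pulled towards zero. The same procedure applies to every main effect and interaction, and to the continuous secondary outcomes.

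**Working it through.** **1. The plan's own figure.** Noncentral F test with noncentrality N × f², 1 and N − 8 degrees of freedom, alpha 0.05. At N = 351 the noncentrality is 351 × 0.0225 = 7.90 and power is 0.8002; at N = 350 power is 0.7991. The stated 351 is reproduced, for complete data.

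**2. Inputs.** From the protocol: eight equal cells, f = 0.15 (a difference of 0.30 SD between the two levels of a factor), alpha 0.05. N = 352 is used for equal cells of 44. Assumed, because the protocol gives no value: proportion missing m = 10–50%; baseline/3-month correlation r = 0.3–0.7; data missing completely at random; normal outcomes with unit variance at each time; imputation from baseline only.

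**3. Factors in the imputation model.** The ANOVA's time-by-training test is a test on change from baseline.

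- Variance the ANOVA sees: V_rep = (1 − m) × 2(1 − r) + m × (1 − r)². Observed changes have variance 2(1 − r); filled ones only (1 − r)².
- Variance that applies: V_true = (1 − r²)/(1 − m) + (1 − r)².
- SE = 2 × √(V/N) in each case, and type I error ≈ 2Φ(−1.96 × √(V_rep/V_true)).

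At r = 0.5 and m = 0.5: V_rep = 0.5 × 1 + 0.5 × 0.25 = 0.625, so the reported SE is 0.084. V_true = 0.75/0.5 + 0.25 = 1.75, so the true SE is 0.141. The ratio is 0.60 and type I error is 2Φ(−1.17) = 24%.

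The formula at r = 0.5 beside a simulation (4,000 runs per setting):

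| Missing | SE ratio, formula | Type I, formula | SE ratio, simulated | Type I, simulated |
|---|---|---|---|---|
| 10% | 0.92 | 7.0% | 0.91 | 7.6% |
| 20% | 0.85 | 9.7% | 0.85 | 9.1% |
| 30% | 0.77 | 13.3% | 0.74 | 14.2% |
| 40% | 0.68 | 18.1% | 0.67 | 18.1% |
| 50% | 0.60 | 24.2% | 0.60 | 24.2% |

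Over r = 0.3–0.7 the simulated type I error is 12.6–15.1% at 30% missing and 22.0–28.8% at 50%. At 20% missing and r = 0.7 it is 10.9%. A random residual added to a single fill does not cure the problem: type I error is still 10.8–13.4% at 30% missing.

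**4. Factors left out.** Type I error stays at 4.5–5.5%. The expected estimate is (1 − m) × 0.30, and power ≈ Φ(estimate/SE − 1.96). At r = 0.5:

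| Missing | Estimate of a true 0.30 | Reported SE | Power, formula | Power, simulated |
|---|---|---|---|---|
| 20% | 0.24 | 0.098 | 69% | 69% |
| 30% | 0.21 | 0.094 | 61% | 59% |
| 50% | 0.15 | 0.084 | 43% | 43% |

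**5. Comparator.** Analysing observed data only keeps type I error at 4.3–5.9% and the SE ratio at 0.97–1.02 throughout. Its simulated power at r = 0.5 is 72%, 65% and 49% at 20%, 30% and 50% missing. Much of the power loss in step 4 therefore comes from the missing data themselves. The dilution of the estimate does not.

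**The case against.** The strongest reply is that the harm is conditional and some of the detail is inferred. Most of that is fair.

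- **Type I error.** A reader might infer that the plan inflates type I error whatever else is done. The protocol does not support that: it does not name the variables in the EM model, and with the factors left out the test keeps its level. This reply does not rescue the plan, because that version biases the effect towards zero.
- **Single imputation.** The text does not say that each value is imputed once. That is the natural reading of EM followed by a plain ANOVA, but a separate analysis plan could add a correction. What stands is that the protocol states a method and an analysis, and the two as stated do not fit together.
- **Other assessments.** The imputation could draw on the post-intervention, 6- and 12-month data. In a smaller simulation (600 runs, assumed correlation of 0.75 between follow-ups, partly observed), this cut type I error at 50% missing from 25% to 18%, and eased the dilution from 0.16 to 0.20 for a true 0.30. At 10–30% missing it made no clear difference to type I error.
- **Attrition.** A reader might infer that the trial itself predicts heavy loss. The Discussion speaks of online interventions in general and lists five measures to encourage adherence, among them reminders and a lottery for completing follow-up. At 10% missing the inflation is modest.
- **Two time points.** A reader might see an error in an ANOVA limited to baseline and 3 months when the Trial design section says "Intervention effects will be tested directly after the intervention and 3, 6 and 12 months later". It is not one: the change from baseline to 3 months is the declared primary outcome.

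**Conclusion.** The point holds in conditional form. On its natural reading, the stated combination of EM filling and ordinary ANOVA gives either an anti-conservative test or a diluted effect, and the protocol does not say which.

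With the training factors in the imputation model, type I error per test is about 6–8%, 9–11%, 13–15% and 22–29% at 10%, 20%, 30% and 50% missing, against a nominal 5%. The highest figures come down if other follow-ups inform the imputation. With the factors left out, a true 0.30 SD becomes about 0.24, 0.21 and 0.15 at 20%, 30% and 50% missing, and power is about 69%, 59% and 43% against the planned 80%.

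The direction of each result follows from the method. The size rests on the assumed attrition and correlation, on normal outcomes and on data missing completely at random. Informative dropout would add bias that these figures do not include.

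**What to change.** In Clinical evaluation, replace the EM fill-in with one of two methods, keeping the 3-month contrast as primary:

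- multiple imputation, with the three training factors and their interactions, baseline drinking and the other assessments in the imputation model, and results combined by Rubin's rules; or
- a likelihood-based mixed model on all observed TLFB data.

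Either serves the intention-to-treat aim already stated. The cost is a change of wording, a little more programming and larger but valid standard errors; no new data are needed.

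Some power lost to missing data will then show openly. With the true SE from step 3 of the working (r = 0.5), power for 0.30 SD is about Φ(0.30/0.116 − 1.96) = 73% at 20% missing, Φ(0.30/0.1225 − 1.96) = 69% at 30% and Φ(0.30/0.141 − 1.96) = 57% at 50%. These approximate what a valid analysis using baseline and 3-month data would give; neither replacement method was simulated.

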### Aims and hypotheses

The aim of the current study is to investigate the effectiveness of three online CBM interventions: attentional bias retraining, alcohol/no-go training (targeting memory bias), and approach bias retraining. Problem drinkers receive 12 sessions of either the active or the placebo version of all three training programs, after completing the first two modules of an evidence-based online cognitive behavioural therapy (CBT) based intervention, *DrinkingLess*[25]*,* consisting of personalised feedback on one’s alcohol use and setting personal goals related to alcohol use, in order to increase motivation to change. The main goal of the study is to test the added effects of the CBM interventions on alcohol use at 3 months after the intervention, with changes in the number of alcoholic drinks consumed in the past two weeks as the primary outcome measure. It is expected that, for each of the CBM interventions, participants in the intervention conditions will show a greater decrease in weekly alcohol use than participants in the placebo conditions. Furthermore, each CBM intervention is hypothesised to decrease or reverse the specific bias it trains and these changes are expected to mediate the effects on alcohol use. Spill-over effects of each specific CBM intervention to other biases will be explored, as will the effects of the joint exposure to the various combinations of CBM interventions. In order to answer the question of “what works for *whom*?”, possible moderators will be examined. In line with dual process models, it is expected that participants with strong automatic biases and/or low working memory capacity and inhibitory control will benefit more from CBM than participants with weaker biases and/or stronger executive functions (as was found for CBM both in addiction [21] and in anxiety [26,27]). A better understanding of the relative contribution of each CBM version on treatment outcome is also expected to come from examining the cost-effectiveness of CBM interventions. Knowledge about the most effective CBM version(s) may have important implications for making choices in the implementation of CBM in health care.

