### Participants and procedure

To ensure the ecological validity of the sample, participants will be recruited through sources that are comparable to how internet interventions are generally promoted in the Netherlands: the *DrinkingLess* website, websites related to alcohol abuse, newspaper articles, a television documentary on CBM for addiction, the website of the ADAPT lab, and word of mouth communication with existing participants. Interested participants are invited to create an account on the intervention website (http://www.test.uva.nl/toptrainingen), after which they read the information letter, a copy of which is automatically sent to them by e-mail. Participants who sign the online consent form then complete a brief screening for eligibility. Participants will be included if they: (a) have an Alcohol Use Disorders Identification Test (AUDIT [30]) score of 8 or above (b) have drunk more than 21 drinks (men) or 14 drinks (women) a week in the past two weeks, as assessed with the Timeline-Follow-Back (TLFB) method (c) are between 18–64 years old (d) have (almost) daily internet access and (e) do not receive professional treatment for problem drinking at the start of the study. Participants with an AUDIT score of >19 receive a message warning them that abrupt abstaining can have mental and physical consequences, and advising them to contact their General Practitioner in case of withdrawal symptoms. Eligible participants then complete the baseline assessment and two modules of *DrinkingLess*. The next day, they are invited to complete the first CBM training session. Participants have three days to complete each session, allowing them to complete the 12 training sessions in about 5 weeks. One day after the last training session, participants are invited to complete the post-intervention assessment. Follow-up assessments are conducted at three, six and twelve months after the intervention. The study has been approved by the Ethics Committee of the psychology department of the University of Amsterdam and registered at the Netherlands Trial register (NTR3875).

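### The one stated model, a baseline/3-month ANOVA for the primary and all continuous secondary outcomes, conflicts with the promised tests at post-intervention, 6 and 12 months and gives no time order for mediation

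*Protocol article*

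**What the plan says.** The Clinical evaluation section gives a single model. It states that main and interaction effects "on the primary and the continuous secondary outcome measures will be analysed with a 2" × 2 × 2 × 2 design, in which the last factor is "2 (time: pre-intervention/3 month follow-up) repeated measures ANOVA". The sentence is not restricted to the primary outcome.

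Four other statements in the protocol bear on it:

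- **Trial design:** "Intervention effects will be tested directly after the intervention and 3, 6 and 12 months later".
- **Participants and procedure:** all four assessments are scheduled. "One day after the last training session, participants are invited to complete the post-intervention assessment", and "Follow-up assessments are conducted at three, six and twelve months after the intervention".
- **Primary and secondary outcome measures:** the primary outcome is "the change in number of drinks consumed in the past 14 days three months after the intervention compared to baseline". The first secondary outcomes listed are "changes in automatic cognitive biases as assessed with the attentional bias, alcohol/no-go and approach bias tasks described above".
- **Aims and hypotheses:** each training should reduce its own bias, and "these changes are expected to mediate the effects on alcohol use".

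The CBM interventions section adds that bias is also measured in a 48-trial block in each of the 12 sessions, in order to see whether it falls under training.

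**The concern.** Two sections disagree on when effects are tested. One names four times; the other fixes a model with room for one of them, and extends that model to every continuous secondary outcome. Until this is settled, the time point behind each secondary claim could be chosen after the data are seen.

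The bias measures are affected most. The trial's explanation of how training works is that bias changes first and drinking follows. A model that compares baseline with 3 months for both takes the two changes over one interval. It cannot separate a fall in bias that reduces drinking from a fall in drinking that reduces bias. It also bypasses the assessment nearest to the end of training, where a training effect on bias should be most visible, and it says nothing on whether effects last to 6 and 12 months.

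**Working it through.** **1. Assessment times against the stated model**

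| Assessment | Scheduled | Test promised (Trial design) | Level of the time factor (Clinical evaluation) |
|---|---|---|---|
| Baseline | yes | reference | yes |
| Post-intervention | yes | yes | no |
| 3 months | yes | yes | yes |
| 6 months | yes | yes | no |
| 12 months | yes | yes | no |

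Four post-baseline tests are promised and one fits the model. Three of four (3/4 = 75%) have no place in it.

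**2. Does the model cover the bias measures?** Reaction-time bias scores are continuous and are listed as secondary outcomes. The Clinical evaluation sentence covers continuous secondary outcomes. So, as written, training effects on bias are tested from baseline to 3 months.

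**3. Time order at 3 months.** The primary outcome counts drinks over the 14 days before the 3-month assessment. A bias score taken at that assessment is recorded at the end of that window, after the drinking it is supposed to explain. A post-intervention score is offered one day after the last session. Taking 3 months as about 13 weeks, the drinking window opens at about 13 − 2 = 11 weeks, so a post-intervention score obtained on schedule precedes it by roughly 11 weeks. The in-session scores are earlier still.

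**4. If bias is not measured at 3 months.** Figure 6, the overview of instruments by assessment, is not available here. If the bias tasks are given at 3 months, step 3 applies. If they are not, the stated ANOVA cannot be run on them. The sentence needs correcting in either case.

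**5. Is the sample size touched?** Inputs from the Sample size section: f = 0.15, alpha 0.05, power 0.8, numerator df = 1; eight groups from the Trial design section. With noncentrality λ = N·f² and denominator df = N − 8:

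- N = 351: λ = 351 × 0.0225 = 7.90, df = 343, power 0.8002.
- N = 350: λ = 350 × 0.0225 = 7.88, df = 342, power 0.7991.

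The smallest N reaching 0.8 is 351, exactly the protocol's figure. As a cross-check, the normal approximation with d = 2f = 0.3 gives 350. The calculation is for one between-subject contrast with 1 df and has no input for the number of assessment times, so this point does not alter it. A sample size under a longitudinal model would need within-person correlations, which the protocol does not give.

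**The case against.** The strongest reply has four parts.

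- **The later data are meant to be used.** The Trial design section commits to testing at all four times. A reader might infer that the post-intervention, 6- and 12-month data will go unused; the protocol does not say so. This stands. The defect is a conflict between two sections.
- **No mediation model is stated.** A reader might infer that the mediator is the 3-month bias score and that the mediation hypothesis therefore cannot be answered. The Clinical evaluation sentence concerns effects of the trainings on outcomes and is silent on mediation, and bias is measured at every session and may be measured again at post-intervention. This stands too: what lacks time order is the stated model, not the data.
- **Imputation.** A reader might infer that neighbouring assessments are thrown away when a 3-month value is missing. The protocol imputes missing endpoints with the EM algorithm without listing the variables used, so this cannot be established.
- **A condensed article leaves secondary models to a fuller document.** This is true of what is absent, and the absence of a mediation or 6- and 12-month model is not the point. But the sentence does more than omit: it assigns the two-time model to all continuous secondary outcomes. A fuller plan would have to override it.

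It is also fair to say that, for the primary outcome, the training-by-time term in a two-time ANOVA tests exactly the declared change from baseline to 3 months.

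**Conclusion.** The point holds as a conflict within the protocol that should be resolved before analysis. Followed literally, the Clinical evaluation section cannot deliver three of the four promised tests, misses the immediate effect of training on bias, and examines bias and drinking over the same interval, so that on its own it gives no time order for the mediation hypothesis. It affects secondary outcomes and the explanatory claim. The primary 3-month test and the sample size of 351 are not affected.

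This rests on reading the Clinical evaluation sentence as written. Which bias tasks are given at which visit could not be confirmed.

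**What to change.** Reconcile the Clinical evaluation and Trial design sections as follows.

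1. Replace the two-time ANOVA by a mixed model for repeated measures, with the baseline value as covariate, time (post-intervention, 3, 6 and 12 months) as a categorical factor, and training-by-time terms.
2. For drinking, keep the 3-month contrast primary and name the 6- and 12-month contrasts as secondary.
3. For the bias outcomes, make the post-intervention contrast the main one.
4. Define the mediator as bias change from baseline up to post-intervention, ahead of the 14-day drinking window at 3 months. If the bias tasks are not given at the post-intervention visit, the assessment block of the last session is the nearest earlier measure; it comes before that session's training block, so it reflects 11 of the 12 sessions.
5. Align the imputation sentence with this model, which uses all observed assessments under a missing-at-random assumption.

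No new data are needed. The cost is revised wording, modest programming and more secondary estimates to report, which should be labelled as secondary.
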